### Modeling the Economic Costs of the Intervention

Decision-analytic modeling will be undertaken to estimate the long-term effectiveness of the intervention compared with usual care. The costs of setting up and providing the intervention are being collected. Ongoing costs will be combined with unit costs to produce the total cost of the intervention over the 24-month study period. Unit costs for health care resources will be calculated from local and national sources and standardized to current prices. Comparisons of the primary outcome measure (individuals achieving BP and TC clinical targets) between baseline and 24-month follow-up interventions will be used to estimate the costs and incremental cost-effectiveness ratios.

The average number of eligible patients per practice will be used to estimate costs at the practice and Clinical Commissioning Group levels. All costs will be for 2016. Salary costs will be taken from Curtis (2015, [27]), and the cost of laboratory tests will be provided by the Leicester Pathology Service. Time to undertake tasks will be modeled with uncertainty in the analysis.

## Results

Baseline data have been extracted from 22 practices (12 controls and 10 interventions; Figure 1) with a reference date of October 30th, 2015. The total number of patients registered at participating practices is 232,639. There are 2721 patients with T2DM meeting the study MA criteria and eligible for the study. Of these 2721, 1067 patients (39.5%; 95% CI 37.7-41.4) had a code for MA or proteinuria in their electronic medical notes.

Biomedical characteristics, current risk factor control, medical history, and current drug prescriptions of the study population are shown in Tables 1-3. The mean age of patients is 62.9 (SD 10.0) years. There are no significant differences in number of male or female patients, and the study population, in keeping with local demographics, is predominantly of South Asian ethnicity (1136/1838 patients, 61.77%). The mean duration of T2DM is 10.5 (SD 7.2) years. Out of 2721 participants, 415 (15.25%) and 739 (27.16%) patients are current smokers and ex-smokers, respectively. Out of 2721 patients, 536 (19.70%) have chronic kidney disease stage 3.

The mean HbA_1c_ is 59.3 (SD 17.4) mmol/mol , mean systolic and diastolic BP (mm Hg) is 134.3 (SD 14.6) and 76.1 (SD 9.5) mm Hg, respectively, and mean TC is 4.1 (SD 0.98) mmol/L. Out of 2721 patients, 630 (23.15%) had achieved a tight BP target of <130/80 mm Hg and 707 patients (25.98%) had achieved a tight TC target of <3.5 mmol/L. Overall, 131 out of 2721 (4.81%) patients achieved all 3 “tight” CV risk factor targets. CV risk factor burden assessed by the prevalence of coronary heart disease, cerebrovascular disease, and peripheral vascular disease increased two-fold in those with eGFR<60 mL/min/1.73 m^2^ compared with those with eGFR≥60 mL/min/1.73 m^2^. Overall, 1076 out of 2721 (39.46%) individuals had a code for MA or proteinuria on their primary care medical record. Out of 2721 patients, 2064 (75.85%) were prescribed a nephroprotective agent, such as an angiotensin-converting enzyme inhibitor or an angiotensin receptor blocker drug, whereas 2070 patients (76.07%) were prescribed a cholesterol-lowering medication, that is, statin therapy.

**Figure 1 figure1:**
[figure not shown]
Recruitment flowchart. T2DM: type 2 diabetes; MA: microalbuminuria.

**Table 1 table1:** Biomedical characteristics of eligible study patients.

Characteristics		Control (N=1299)	Intervention (N=1422)	Total (N=2721)	*P* value
Age in years, mean (SD)		62.8 (10.1)	62.9 (9.9)	62.9 (10.0)	.63
**Age category, n (%)**					
	<30 years	4 (0.31)	3 (0.21)	7 (0.26)	
	30-44 years	67 (5.16)	63 (4.43)	130 (4.78)	
	45-65 years	623 (47.96)	712 (50.07)	1335 (49.06)	
	>65 years	605 (46.57)	644 (45.29)	1249 (45.90)	
**Gender, n (%)**					**.27**
	Male	776 (59.74)	820 (57.67)	1596 (58.65)	
	Female	523 (40.26)	602 (42.33)	1125 (41.35)	
**Ethnicity, n (%)**					**<.001**
	White	380 (38.31)	195 (23.0)	575 (31.27)	
	Black	45 (4.54)	17 (2.01)	62 (3.37)	
	Asian	516 (52.02)	620 (73.20)	1136 (61.77)	
	Mixed	14 (1.41)	6 (0.71)	20 (1.09)	
	Other	37 (3.73)	9 (1.06)	46 (2.50)	
**Smoking status, n (%)**					**.64**
	Nonsmoker	750 (57.74)	817 (57.45)	1567 (57.59)	
	Current smoker	205 (15.78)	210 (14.77)	415 (15.25)	
	Ex-smoker	344 (26.48)	395 (27.78)	739 (27.16)	
Duration of T2DM^a^ in years, mean (SD)		10.62 (7.31)	10.31 (7.14)	10.46 (7.22)	.27
HbA_1c_^b^ in mmol/mol, mean (SD)		59.8 (18.1)	58.9 (16.7)	59.3 (17.4)	.14
HbA_1c_<53 mmol/mol, n (%)		546 (42.03)	618 (43.46)	1164 (42.78)	.45
HbA_1c_<58.5 mmol/mol, n (%)		755 (58.12)	849 (59.70)	1604 (58.95)	.39
Total cholesterol in mmol/L, mean (SD)		4.1 (1.0)	4.1 (0.94)	4.1 (0.98)	.05
Total cholesterol<3.5 mmol/L, n (%)		335 (25.79)	372 (26.16)	707 (25.98)	.81
Total cholesterol<5 mmol/L, n (%)		1075 (82.76)	1211 (85.16)	2286 (84.01)	.07
Systolic BP^c^ in mm Hg, mean (SD)		134.0 (15.0)	134.5 (14.2)	134.3 (14.6)	.82
Diastolic BP in mm Hg, mean (SD)		76.7 (9.7)	75.4 (9.2)	76.1 (9.5)	<.001
BP<130/80 mm Hg, n (%)		320 (24.63)	320 (22.50)	640 (23.52)	.19
BP<140/80 mm Hg, n (%)		608 (46.81)	670 (47.12)	1278 (46.97)	.87
eGFR^d^ in mL/min, median (IQR^e^)		81.0 (62.0-90.0)	85.0 (66.0-90.0)	83.0 (64.0-90.0)	.047
**CKD^f^ Stage 3, n (%)**		260 (20.02)	276 (19.41)	536 (19.70)	.06
	Stage 3a	34 (13.08)	30 (10.87)	64 (11.94)	.38
	Stage 3b	22 (8.46)	13 (4.71)	35 (6.53)	.07
CKD Stage 4, n (%)		33 (2.54)	21 (1.48)	54 (1.98)	.05
CKD Stage 5, n (%)		20 (1.54)	13 (0.91)	33 (1.21)	.14
**Medical history, n (%)**					
	Myocardial infarction	97 (7.47)	89 (6.26)	186 (6.84)	.21
	Acute coronary syndrome	51 (3.93)	57 (4.01)	108 (3.97)	.91
	Angina	120 (9.24)	132 (9.28)	252 (9.26)	.97
	Ischemic heart disease	249 (19.17)	264 (18.57)	513 (18.85)	.68
	Transient ischemic attack	66 (55.08)	35 (2.46)	101 (3.71)	<.001
	Stroke	46 (3.54)	55 (3.87)	101 (3.71)	.65
	Peripheral vascular disease	48 (3.70)	34 (2.39)	82 (3.01)	.047
	Revascularization procedure	92 (7.08)	40 (2.81)	132 (4.85)	<.001
	Bypass graft	47 (3.62)	53 (3.73)	100 (3.68)	.88
**Number of study risk factors controlled, n (%)^g^**					**.21**
	0	336 (25.87)	337 (23.70)	673 (24.73)	
	1	579 (44.57)	680 (47.82)	1259 (46.27)	
	2	309 (23.79)	336 (23.63)	645 (23.70)	
	3	70 (5.39)	61 (4.29)	131 (4.81)	
MA^h^/proteinuria code, n (%)		410 (31.56)	666 (46.84)	1076 (39.54)	<.001

^a^T2DM: type 2 diabetes.

^b^HbA_1c_: glycated hemoglobin.

^c^BP: blood pressure.

^d^eGFR: estimated glomerular filtration rate.

^e^IQR: interquartile range.

^f^CKD: chronic kidney disease.

^g^HbA_1c_ <7.5% (58.5 mmol/mol), total cholesterol <3.5 mmol/L, BP <130/80 mm Hg.

^h^MA: microalbuminuria.

**Table 2 table2:** Vascular burden between patient groups categorized by chronic kidney disease stages.

Disease characteristic		Patients with MA^a^ and eGFR^b^ <60			Patients with MA and eGFR>60		
		Control (N=280)	Intervention (N=258)	Total (N=538)	Control (N=1019)	Intervention (N=1164)	Total (N=2183)
**Cardiovascular disease, n (%)**							
	Myocardial infarction	33 (11.8)	29 (11.2)	62 (11.5)	63 (6.18)	58 (4.98)	121 (5.54)
	Acute coronary syndrome	19 (6.8)	16 (6.2)	35 (6.5)	32 (3.14)	41 (3.52)	73 (3.34)
	Angina	38 (13.6)	30 (11.6)	68 (12.6)	81 (7.95)	101 (8.68)	182 (8.34)
	Ischemic heart disease	78 (27.9)	75 (29.1)	153 (28.4)	169 (16.58)	186 (15.98)	355 (16.26)
	Coronary artery bypass graft	18 (6.4)	16 (6.2)	34 (6.3)	29 (2.58)	36 (3.09)	65 (2.98)
**Cerebrovascular disease, n (%)**							
	Transient ischemic attack	19 (6.8)	10 (3.9)	29 (5.4)	47 (4.61)	25 (2.15)	72 (3.30)
	Stroke	15 (5.4)	16 (6.2)	31 (5.8)	30 (2.94)	38 (3.26)	68 (3.11)
	Peripheral vascular disease	21 (7.5)	16 (6.2)	37 (6.9)	27 (2.65)	18 (1.55)	45 (2.06)
	Hypertension (BP^c^>130/80)	80 (28.6)	81 (31.4)	161 (29.9)	236 (23.16)	235 (20.19)	471 (21.58)
	Hyperlipidemia (TC^d^>4.0)	125 (44.6)	110 (42.6)	235 (43.7)	482 (47.30)	504 (43.30)	986 (45.17)

^a^MA: microalbuminuria.

^b^eGFR: estimated glomerular filtration rate.

^c^BP: blood pressure.

^d^TC: total cholesterol.

**Table 3 table3:** Drug prescribing in eligible study individuals at baseline.

Drug	Control (N=1299), n (%)	Intervention (N=1422), n (%)	Total (N=2721), n (%)	*P* value
Long-acting insulin	225 (17.32)	268 (18.85)	493 (18.12)	.30
Short-acting insulin	92 (7.08)	123 (8.65)	215 (7.90)	.13
Metformin	926 (71.29)	971 (68.28)	1897 (69.72)	.09
Sulphonylurea	422 (32.49)	434 (30.52)	856 (31.46)	.27
Dipeptidyl peptidase-4 (DPP-4)	205 (15.78)	228 (16.03)	433 (15.91)	.86
Thiazolidinediones (TZD)	78 (6.00)	28 (1.97)	106 (3.90)	<.001
Glucagon-like peptide-1 receptor antagonist (GLP-1 RA)	56 (4.31)	39 (2.74)	95 (3.49)	.03
Sodium glucose transporter-1 inhibitor (SGLT-2i)	28 (2.16)	20 (1.41)	48 (1.76)	.14
Meglitinide	220 (16.94)	311 (21.87)	531 (19.51)	.001
Calcium channel blocker (CCB)	524 (40.34)	592 (41.63)	1116 (41.01)	.49
Diuretic	388 (29.87)	412 (28.97)	800 (29.40)	.61
Angiotensin-converting enzyme (ACE) inhibitor	666 (51.27)	713 (50.14)	1379 (50.68)	.56
Angiotensin receptor blocker (ARB)	349 (26.87)	336 (23.63)	685 (25.17)	.05
Beta blocker	376 (29.95)	407 (28.62)	783 (28.78)	.85
Alpha blocker	393 (30.25)	455 (32.00)	848 (31.17)	.23
Aspirin	393 (30.25)	455 (32.00)	848 (31.17)	.33
Clopidogrel	74 (5.70)	76 (5.34)	150 (5.51)	.69
Statin	959 (73.83)	1111 (78.13)	2070 (76.07)	.01
Fibrate	29 (2.23)	32 (2.25)	61 (2.24)	.98
Ezetimibe	26 (2.00)	37 (2.60)	63 (2.32)	.30
Warfarin	66 (5.08)	79 (5.56)	145 (5.33)	.58

## Discussion

### Overview

This paper describes the design and baseline characteristics of a pragmatic cluster RCT that will investigate the effectiveness of a multifactorial intervention. The study’s achievements thus far include the following: establishing the infrastructure for the trial, recruitment of the required number of GP practices, provision of training for HCPs at intervention practices, and baseline data extraction. Analysis of the baseline data shows poor coding levels of individuals meeting the diagnostic criteria for MA within their medical record. Subgroup analysis by eGFR highlights the increased vascular burden in patients with kidney disease.

### Principal Findings

MA is an easily available integrated marker, suggesting subclinical generalized involvement of the vascular system, predisposing individuals with T2DM to increased risk of CV disease. Evaluation of abnormal urinary albumin excretion through urinary ACR in individuals with T2DM is a specific and cost-effective method to help identify individuals who can benefit from additional intensive, targeted interventions involving tight CV risk factor control [3,28]. However, despite the plethora of evidence, UK National Audit data from 2015 to 2016 showed that only 40.2% people with T2DM were reaching all 3 treatment targets [29] (HbA_1c_<58 mmol/mol, BP<140/80 mm Hg, and TC<5 mmol/L). Although we used tighter risk factor targets in our study, which may not conform to targets set out by practicing clinicians in primary care (eg, UK QOF targets), it can be argued that the nature of a high-risk state such as T2DM with MA deserves stricter cardio-metabolic control to achieve greater CV mortality and morbidity benefits [3,28,30]. However, individualization of therapy must take precedence as emphasized in the National Institute For Health and Care Excellence (NICE) guidelines for T2DM in the United Kingdom [2] and in the new 2017 American Diabetes Association statement on standards of medical care in diabetes [31], which encourages clinicians to use a pragmatic approach and be cognizant of the “risk-benefits” while using treatments to minimize CV risk. Accordingly, although our baseline data in this high-risk population suggest “adequate to satisfactory” performance in achieving tight cardio-metabolic risk factors targets, prescribing patterns particularly relating to nephroprotective agents and statin therapy and achieving all “prescribed” care processes such as “coding for MA” could be improved.

A number of reasons may explain why a high proportion of individuals do not achieve cardio-metabolic targets in primary care, including clinical inertia, aiming only for “prescribed” QOF targets [32,33], lack of time for treating complex patients, gaps in clinician knowledge, and the need for a well-organized health care system to manage chronic conditions [34]. However, improvements in clinical care processes and targeted control of CV risk factors in high-risk individuals with T2DM and MA have recognized benefits and should be pursued without delay and with commitment, both from the perspective of the HCP and the affected individual [3,30]. Our hypothesis was that a multifaceted, multifactorial intervention including the use of an electronic “Prompt” readily available and visible to the treating HCP during “limited” consultation times would serve as an “aide-memoire” to intensify treatment targets and improve clinical outcomes.

A cluster randomized design was chosen to avoid contamination [35] which may have occurred if it was at the patient level. Furthermore, HCPs could face conflict if they were to deliver a purposeful intensive intervention only to certain individuals within their population.

The GP prompt study, to our knowledge, is the largest RCT assessing the effectiveness of a practice-level intervention to support management of a multiethnic population diagnosed with T2DM and MA. Baseline data give contemporary estimates for adherence to best practice risk factor targets and the increased vascular burden in these affected individuals.

### Limitations

An identified weakness of this trial may relate to the chosen method of data collection. To allow collection of large amounts of data and cluster randomization at the practice level, Read-coded primary care data are being collected using MIQUEST. The accuracy of the data and their usefulness as resource for study are therefore dependent on the coding practices of individual clinicians in individual practices. For example, level of coding within primary care for ethnicity has previously been found to be poor [36]. Our baseline data suggest that although recording of ethnicity data has improved, there remains significant variation between practices. This lack of complete data may limit our ability to perform secondary subgroup analysis to study interracial variations [37].

Anecdotal evidence suggests that coding quality for MA within primary care data is poor. Putative factors may include requirement for more than one sample to make a diagnosis, which may cause delays in diagnosis; infrequent testing and recall; and lack of recognition of MA as an important “CV risk marker.” Furthermore, it is likely that recommended processes of care that are performed frequently (BP, HbA_1c_, and lipid checks) may be more diligently recorded than those recommended and/or performed less frequently (eg, MA, foot examination). To account for this, we used pragmatic inclusion criteria based on international guidelines for MA [2]. We used a definition of 2 abnormal ACR values (2.5 mg/mmol for men, >3.5 mg/mmol for women) >90 days but <180 days apart [38]. Using this definition, only 1076 out of 2721 patients (39.54%) with 2 abnormal ACR values (>2.5 in males and >3.5 females) on 2 occasions >90 days and <180 days apart were coded as having MA or overt proteinuria. We were not able to exclude patients with proteinuria or urinary tract infection as per national guidance because of the methodology by which such data are coded. Despite this, prevalence rates for MA within the study population are broadly in line with other large contemporary population–based studies [39].

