**Methods:**

A cluster randomized trial will be performed where the primary outcome is the proportion of eligible patients meeting tight cardiovascular risk factor targets, including systolic and diastolic blood pressure (BP; BP<130/80 mm Hg) and total cholesterol (TC; TC<3.5 mmol/L) at 24 months. Secondary outcomes include proportion of patients with glycated hemoglobin (HbA_1c_) <58 mmol/mol (7.5%), change in medication prescribing, changes in microalbuminuria and renal function (estimated glomerular filtration rate, eGFR), incidence of major adverse CV events and mortality, and coding accuracy. Cost-effectiveness of the intervention will also be assessed.

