### Patient Inclusion Criteria

Patient-level data were extracted for individuals aged between 17 and 76 years with a Read code for T2DM and MA or overt proteinuria on their clinical record, or individuals with T2DM and albumin-creatinine ratio (ACR)>2.5 in males and >3.5 in females on 2 consecutive occasions of >90 days and <180 days apart, having excluded a urinary tract infection [2].

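### The article defines the 2721 patients in two conflicting ways, so the denominator of the 39.54% coding figure is unsettled and the stated exclusion of urinary tract infection is contradicted

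*Protocol article*

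**What the plan says.** **Entry route.** Patient Inclusion Criteria gives two alternatives. Data were extracted for people "with a Read code for T2DM and MA or overt proteinuria on their clinical record, or individuals with T2DM and albumin-creatinine ratio" above sex-specific thresholds. The ACR route is completed by "on 2 consecutive occasions of >90 days and <180 days apart, having excluded a urinary tract infection". On this wording a code is sufficient by itself.

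**Size of the cohort.** Results states: "There are 2721 patients with T2DM meeting the study MA criteria and eligible for the study". The only full statement of those criteria in Methods is the code-or-ACR rule.

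**The same cohort in Limitations.** Here the rule is put differently: "We used a definition of 2 abnormal ACR values", with no code-only route. Applying it, the article reports "only 1076 out of 2721 patients (39.54%) with 2 abnormal ACR values" as coded for microalbuminuria or overt proteinuria.

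**Urinary tract infection.** The inclusion criteria say "having excluded a urinary tract infection". Limitations says "We were not able to exclude patients with proteinuria or urinary tract infection as per national guidance". Overt proteinuria is also an entry route in the first section and something that could not be excluded in the second.

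**Use of the figure.** The Methods paragraph of the abstract ends its list of secondary outcomes with "and coding accuracy". The 39.54% appears in the abstract's Results and in Table 1, and the Discussion relies on it when it calls coding poor.

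**The concern.** A coding-completeness rate needs a denominator defined independently of the code: patients who have the condition on laboratory evidence, whether or not anyone coded it. If a code alone admits a patient, every such patient is counted as coded by definition, in numerator and denominator alike. The proportion then mixes how well practices code ACR-confirmed disease with how many patients were admitted only because they were coded.

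This affects a headline baseline result and, if the same denominator is carried forward, a named secondary outcome. The UTI conflict is a separate fault. It does not create the denominator problem, but it means the population stated in Methods is not the one Limitations says was extracted.

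**Working it through.** **1. Reproduce the article's figure.** Table 1 gives 410 coded of 1299 in control and 666 of 1422 in intervention.

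- 410 + 666 = 1076; 1299 + 1422 = 2721.
- 1076/2721 = 39.54%, Wald 95% CI 37.7% to 41.4%. This matches Table 1, Limitations and the interval printed in Results.
- Results also prints 1067 for the same count. 1067/2721 = 39.21%, which does not match the 39.5% beside it, so a transposition of 1076 is likely. It prints 39.46% for 1076/2721 as well, which is not the quotient. I use 1076.

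**2. Compare the two definitions.**

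| | Patient Inclusion Criteria | Limitations |
|---|---|---|
| Route into the 2721 | code alone, or two raised ACRs | two abnormal ACRs |
| UTI | excluded (ACR route) | could not be excluded |
| Overt proteinuria code | admits the patient | could not be excluded |

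The first row can be harmonised only if every one of the 1076 coded patients also had two qualifying ACRs more than 90 and fewer than 180 days apart. The article does not say so. Limitations cites infrequent testing and recall, which makes it less likely. The second row cannot be harmonised.

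**3. Consequence if the inclusion criteria govern.** The uncoded patients, 2721 − 1076 = 1645, must all have entered by ACR. Let c be the number who entered by code alone. Coding among ACR-qualified patients is then

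(1076 − c) / (2721 − c),

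which falls as c rises. The article does not give c, so these values are assumptions:

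| c (assumed) | Calculation | Rate |
|---|---|---|
| 0 | 1076/2721 | 39.5% |
| 100 | 976/2621 | 37.2% |
| 300 | 776/2421 | 32.1% |
| 600 | 476/2121 | 22.4% |
| 1076 (limit) | 0/1645 | 0% |

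So 39.54% is the upper bound, reached only at c = 0.

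**4. By arm, as illustration.** The reported rates are 31.56% and 46.84%, a gap of 15.3 points. If half the coded patients in each arm also met the ACR rule (assumed), control becomes 205/(205 + 889) = 205/1094 = 18.7% and intervention 333/(333 + 756) = 333/1089 = 30.6%, a gap of 11.8 points. Both the level and the contrast depend on the unreported split.

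**5. Consequence if Limitations is literally right.** Then c = 0, 39.54% is coded patients over two-ACR patients, and there is no circularity. Patient Inclusion Criteria would then misstate who was eligible.

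**The case against.** The strongest reply is that the denominator problem is conditional. It needs the inclusion criteria to be the operative rule and at least one patient to have entered by code alone. That stands, and nothing in the document favours c = 100, 300 or 600 over zero.

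Second, the article never defines coding accuracy. It names it once, in the abstract, omits it from Primary and Secondary Outcomes, and presents 39.54% as a baseline description. An operational definition may sit in a fuller document. That also stands: what is visible is a baseline proportion with an unsettled denominator, not a proven defect in the outcome's definition.

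Third, the UTI limitation is openly disclosed. That is fair, but the disclosure does not correct a criterion that Methods still states as applied.

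A reader might go further and infer three things that the documents do not support:

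- **That the intervention will inflate numerator and denominator together.** This requires membership to be re-derived after the prompt went live on November 1, 2015. The baseline reference date is October 30, 2015, and the article does not say whether the cohort is then fixed or re-extracted. Nor does it list improved coding among the intervention's functions.
- **That code-only entrants are unbalanced between arms.** Coding differs by arm (P<.001), but that does not show how many coded patients lacked two ACRs.
- **That the primary outcome is biased.** The same extraction rule is described for both arms, and no such bias is shown.

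What survives is a conflict between printed statements. An analysis plan could say which rule was applied, but one section would still need correcting.

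**Conclusion.** The contradiction is certain for UTI. For entry route it holds unless c = 0, which the article does not state. One of the two sections therefore has to be corrected on UTI, and on entry route the article must either correct one or state that c was zero.

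The effect on the coding figure is conditional. Under the inclusion criteria as written, 39.54% is an upper bound and the rate among ACR-qualified patients could lie anywhere below it. Under Limitations as written, it stands unchanged. The article gives no basis for a point estimate between these.

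Any correction to the overall baseline figure is downward, so the qualitative message that coding is poor would not be reversed. What is uncertain is how poor it is, how far the arms differ at baseline, and what a later coding-accuracy result would measure. The point merits correction but does not threaten the main trial comparison.

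**What to change.** - State one eligibility rule, the one the extraction query applied, and use it in both sections. If UTI could not be excluded, remove the exclusion from Patient Inclusion Criteria or mark it as intended but not carried out. Clarify the position of overt proteinuria in the same edit.
- Report, by arm, how many of the 2721 entered by code only, by ACR only, and by both.
- Calculate coding accuracy as coded patients over all patients with two qualifying ACRs, regardless of code, with membership fixed at the baseline extraction so that later coding cannot alter the denominator. Report code-only patients separately.
- Correct the count of 1067 and the 39.46% in Results while editing.

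The cost is wording and a re-tabulation, provided the extract holds the dated ACR results that the inclusion rule needs. The article does not confirm this, so it should be checked first. The denominator may shrink and the coding figure may fall. A sensitivity analysis of the primary outcome in ACR-qualified patients is optional.
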